**→ *Go through Informed Consent process and document informed consent on form.***

Section 1: Background

Interviewer:

→ I would like to begin our discussion by asking you some questions about yourself.

| **No.** | **Questions and Filters** | **Coding Categories** | **Codes** | **Skip to:** | **VARIABLE** |
| --- | --- | --- | --- | --- | --- |
| Q101 | Sex or gender of the participant: | Male  Female | 1  2 |  | GENDER |
| Q102 | How long have you lived in your current location?  **→** PROBE: A place where you spend at least 2 nights per week. Note that if participant has lived in the current location for his/her entire life, please enter the participant’s age here. | __ __ YEARS  __ __ MONTHS |  | **If Years is ≥ 2, then enter 0 for Months** | LIVE_D_Y  LIVE_D_M |
| Q103 | Where do you usually stay? | IN A HOME WITH MY FAMILY  IN MY OWN RENTED ROOM OR HOUSE  IN A RENTED ROOM/HOUSE WITH FRIENDS (GHETTO)  STREET  PLACE OF WORK OR BUSINESS  IN A CAMP  OTHER _____________________ | 1  2  3  4  5  6  7 |  | STAY_LOC  STAY_S |
| Q104 | Are you currently a student? | NO  YES | 0  1 |  | EDU_NOW |
| Q105 | What is the highest level of school you have completed? | NO FORMAL EDUCATION  STANDARD 4 OR LESS  STANDARD 5-7  FORM ONE  FORM TWO  FORM THREE  FORM FOUR  GREATER THAN FORM FOUR | 1  2  3  4  5  6  7  8 |  | EDUCOMP |
| Q106 | Have you ever been married? | NO  YES | 0  1 |  | MARRIED |
| Q107 | How many children have you had? | NO CHILDREN  __ __ # CHILDREN | 0 | **Q111** | CHILD_EV |
| Q108 | How many of these children are still living? | NO CHILDREN  __ __ # CHILDREN | 0 | **Note that # cannot be > response to Q107** | CHILD_LV |
| Q109 | Do you own any of the following items?  FOAM MATTRESS  BEDFRAME  COOKING POTS  CELL PHONE  RADIO  TELEVISION  COMPUTER  BICYCLE  MOTORBIKE  CAR | NO  YES | 0  1 |  | ASSET_FM  ASSET_BF  ASSET_CKP  ASSET_CELL  ASSET_R  ASSET_TV  ASSET_CMP ASSET_BC  ASSET_MB  ASSET_CR |
| Q110 | What is your role in this camp? | CHAIRPERSON  ASSISTANT CHAIRPERSON  SECRETARY  TREASURER  MEMBER  OTHER _____________________ | 1  2  3  4  5  6 |  | CAMPROLE  CMPROLE_S |
| Q111 | Are there other camps that you visit regularly? | NO  YES | 0  1 | **Q201** | CAMPHNG |
| Q112 | What are the names of these camps?  Note: If participant is a member of more than 2 other camps, separate these camp names with a comma. | OTHER CAMPS VISITED: ____________________________ |  |  | CMPHNG_S |
| Q113 | How often do you go to hang out at these other camps? | EVERY DAY  SEVERAL TIMES A WEEK  ONE TIME PER WEEK  COUPLE TIMES A MONTH  ONE TIME PER MONTH  LESS THAN ONCE A MONTH  NEVER | 1  2  3  4  5  6  7 |  | CMPHNG_F |

Section 2: State Hope Scale

*Interviewer:*

**→** Now, I would like to ask some questions about how you think about yourself right now. *Please take a few moments to focus on yourself and what is going on in your life at this moment.* I will read some statements and will ask you to respond with whether you strongly agree, agree, disagree, or strongly disagree with each statement. Now, I would like to ask you if you agree with the statement…

| **No.** | **Questions and Filters** | **Coding Categories** | **Codes** | **Skip to:** | **VARIABLE** |
| --- | --- | --- | --- | --- | --- |
| Q201 | At the present time, I am energetically pursuing my goals | STRONGLY AGREE  AGREE  DISAGREE  STRONGLY DISAGREE | 1  2  3  4 |  | HOPE1 |
| Q202 | There are lots of ways around any problem that I am facing right now | STRONGLY AGREE  AGREE  DISAGREE  STRONGLY DISAGREE | 1  2  3  4 |  | HOPE2 |
| Q203 | Right now I see myself as being pretty successful. | STRONGLY AGREE  AGREE  DISAGREE  STRONGLY DISAGREE | 1  2  3  4 |  | HOPE3 |
| Q204 | I can think of many ways to reach my current goals. | STRONGLY AGREE  AGREE  DISAGREE  STRONGLY DISAGREE | 1  2  3  4 |  | HOPE4 |
| Q205 | At this time, I am meeting the goals that I have set for myself. | STRONGLY AGREE  AGREE  DISAGREE  STRONGLY DISAGREE | 1  2  3  4 |  | HOPE5 |

Section 3: Future Orientation

*Interviewer:*

**→** Now would like to ask you some questions about how you view your life and the future. I will read you some statements and I would like you to respond with whether the statement is never true, sometimes true, often true, or always true.

| **No.** | **Questions and Filters** | **Coding Categories** | **Codes** | **Skip to:** | **VARIABLE** |
| --- | --- | --- | --- | --- | --- |
| Q301 | I think about how things might be in the future. | NEVER TRUE  SOMETIMES TRUE  OFTEN TRUE  ALWAYS TRUE | 1  2  3  4 |  | FUTUR1 |
| Q302 | I can see my life 10 years from now. | NEVER TRUE  SOMETIMES TRUE  OFTEN TRUE  ALWAYS TRUE | 1  2  3  4 |  | FUTUR2 |
| Q303 | I think often about what tomorrow may bring. | NEVER TRUE  SOMETIMES TRUE  OFTEN TRUE  ALWAYS TRUE | 1  2  3  4 |  | FUTUR3 |
| Q304 | Before making a decision I weigh the good versus the bad. | NEVER TRUE  SOMETIMES TRUE  OFTEN TRUE  ALWAYS TRUE | 1  2  3  4 |  | FUTUR4 |
| Q305 | I think about the consequences before I do something | NEVER TRUE  SOMETIMES TRUE  OFTEN TRUE  ALWAYS TRUE | 1  2  3  4 |  | FUTUR5 |
| Q306 | I like to plan things out one step at a time | NEVER TRUE  SOMETIMES TRUE  OFTEN TRUE  ALWAYS TRUE | 1  2  3  4 |  | FUTUR6 |
| Q307 | I make decisions and act without thinking about the big picture | NEVER TRUE  SOMETIMES TRUE  OFTEN TRUE  ALWAYS TRUE | 1  2  3  4 |  | FUTUR7 |
| Q308 | I think things work out better when you’ve planned for them in advance | NEVER TRUE  SOMETIMES TRUE  OFTEN TRUE  ALWAYS TRUE | 1  2  3  4 |  | FUTUR8 |
| Q309 | I run through all possible outcomes of a decision in my mind before I decide what to do | NEVER TRUE  SOMETIMES TRUE  OFTEN TRUE  ALWAYS TRUE | 1  2  3  4 |  | FUTUR9 |
| Q310 | I don’t think it’s worth it to worry about what I can’t predict | NEVER TRUE  SOMETIMES TRUE  OFTEN TRUE  ALWAYS TRUE | 1  2  3  4 |  | FUTUR10 |
| The next few questions also ask you about how you view life and the future. For these items I will ask you to respond with whether you strongly agree, agree, disagree, or strongly disagree with each statement. | | | | | |
| Q311 | In uncertain times, I usually expect the best. | STRONGLY DISAGREE  DISAGREE  NEITHER AGREE NOR DISAGREE  AGREE  STRONGLY AGREE | 1  2  3  4  5 |  | LOT1 |
| Q312 | If something can go wrong for me it will. | STRONGLY DISAGREE  DISAGREE  NEITHER AGREE NOR DISAGREE  AGREE  STRONGLY AGREE | 1  2  3  4  5 |  | LOT2 |
| Q313 | I’m always optimistic about my future. | STRONGLY DISAGREE  DISAGREE  NEITHER AGREE NOR DISAGREE  AGREE  STRONGLY AGREE | 1  2  3  4  5 |  | LOT3 |
| Q314 | I hardly ever expect things to go my way. | STRONGLY DISAGREE  DISAGREE  NEITHER AGREE NOR DISAGREE  AGREE  STRONGLY AGREE | 1  2  3  4  5 |  | LOT4 |
| Q315 | I rarely count on good things happening to me. | STRONGLY DISAGREE  DISAGREE  NEITHER AGREE NOR DISAGREE  AGREE  STRONGLY AGREE | 1  2  3  4  5 |  | LOT5 |
| Q316 | Overall, I expect more good things to happen to me than bad. | STRONGLY DISAGREE  DISAGREE  NEITHER AGREE NOR DISAGREE  AGREE  STRONGLY AGREE | 1  2  3  4  5 |  | LOT6 |

Section 4: Social Cohesion

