| Q1238 | Has FRIEND 2 discouraged you from having more than one sexual partner at the same time? | NO  YES | 0  1 |  | MCPADVF2 |
| Q1239 | Do you think FRIEND 2 hits his sexual partner? | NO  YES | 0  1 | **ASK ONLY IF Q1227 = 1** | IPVF2 |
| Q1240 | Do you think FRIEND 2 thinks there are some situations in which it’s ok to hit his sexual partner? | NO  YES | 0  1 | **ASK ONLY IF Q1227 = 1** | IPVINJF2 |
| Q1241 | Do you think FRIEND 1 gets hit by her sexual partner? | NO  YES | 0  1 | **ASK ONLY IF Q1227 = 2** | VVF2 |
| Q1242 | Do you think FRIEND 2 thinks there are some situations in which it’s ok for her to be hit by her sexual partner? | NO  YES | 0  1 | **ASK ONLY IF Q1227 = 2** | VVINJF2 |
| Q1243 | Has FRIEND 2 discouraged you from hitting your sexual partner? | NO  YES | 0  1 | **ASK ONLY IF Q101 = 1** | IPVADVF2 |
| Q1244 | Has FRIEND 2 encouraged you to request that your sexual partner not hit you? | NO  YES | 0  1 | **ASK ONLY IF Q101 = 2** | = |
| Q1245 | Do you think FRIEND 2 ever had an HIV test? | NO  YES | 0  1 |  | HIVTSTF2 |
| Q1246 | Do you think FRIEND 2 thinks that he/she should have an HIV test? | NO  YES | 0  1 |  | HIVINJF2 |
| Q1247 | Has FRIEND 2 encouraged you to get an HIV test? | NO  YES | 0  1 |  | HIVADVF2 |

Section 13: Attitudes towards HIV Risk Behaviors and Intimate Partner Violence

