***Interviewer:***

→ Now I would like to ask some more personal questions about you and your relationships. Please remember that your answers will be confidential.

| **No.** | **Questions and Filters** | **Coding Categories** | **Codes** | **Skip to:** | **VARIABLE** |
| --- | --- | --- | --- | --- | --- |
| Q1401 | Have you ever had sex?  • Vaginal sex is when a man puts his penis in the vagina of a woman; [some people call this [Swahili term].  • Anal sex is when a man puts his penis in the rectum of a man or a woman; [some people call this [Swahili term]. | NO  YES | 0  1 | **Q1409 and then AND SKIP to SECTION 16** | SEX_EVR |
| Q1402 | How old were you when you had sex for the first time? If you can’t recall the exact age, please give a best estimate. | __ __ YEARS  DON’T KNOW | 88 |  | SEX_AGE |
| Q1403 | How would you describe the first time that you had sex? Would you say that you wanted to have sex, you did not want to have sex but it happened anyway, or were you forced to have sex? | WANTED TO HAVE SEX  DID NOT WANT TO HAVE SEX BUT HAPPENED ANYWAY  WAS FORCED TO HAVE SEX | 1  2  3 |  | SEX_1DES |
| Q1404 | Did you experience any of the following types of situations the first time you had sex?  VERBAL THREATS  PHYSICAL THREATS  PHYSICAL FORCE/HOLDING DOWN  BEATING  HUMILIATING OR DEGRADING SEX ACTS | NO  YES | 0  1 |  | SEX1_VER  SEX1_PHY  SEX1_FRC  SEX1_DEG |
| Q1405 | In total, how many people have you ever had sex with in your lifetime? | __ __ # PERSONS |  | *Note that if this value is less than 3, the participant will only be asked about the corresponding # of partners in the Sexual Network Section | SEXE_NUM |
| Q1406 | In total, how many people have you had sex with in the past 12 months?  This includes people you had sex with only once and people you have had sex with regularly, such as a spouse or someone you live with.  If you can’t recall the exact number, please give a best guess. | NONE  __ __ # PERSONS | 0 |  | SXP12_NUM |
| Q1407 | How many of these partners were women and how many were men? | WOMEN___________  MEN___________ |  | **ASK ONLY IF Q100 = 1**  ***This should total Q1406** | MSM_NUM |
| Q1408 | In general, how would you consider your chances of getting HIV/AIDS? Are they small, moderate, great, or no risk at all? | NO RISK AT ALL  SMALL  MODERATE  GREAT | 1  2  3  4 |  | HIVRISK |
| Q1409 | Have you ever had a test for HIV/AIDS? | NO  YES  DON’T KNOW | 0  1  88 | **Q1501 (UNLESS Q1401 =0)** | TESTHIV |

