| Q1540 | | Of these (Response from Q1539) times, how many times would you say you used a condom? | _____________ | |  |  | NUMCND_P2 |
| Q1541 | | Did you ever give PARTNER 2 money in exchange for having sex with you? | NO  YES | | 0  1 |  | GIVFSP_P2 |
| Q1542 | | Did PARTNER 2 ever give YOU money in exchange for having sex? | NO  YES | | 0  1 |  | RECFSP_P2 |
| Q1543 | | Did you use a condom the last time money was given or exchanged for sex with PARTNER 2? | NO  YES | | 0  1 | **ASK ONLY IF either Q1542 or Q1543 =1** | CNDM_P2 |
| Q1544 | | The last time you had sex with PARTNER 2, did you drink alcohol before or during sex | NO  YES | | 0  1 |  | DRNK1_P2 |
| Q1545 | | The last time you had sex with PARTNER 2, did PARTNER 2 drink alcohol before or during sex with you? | NO  YES  DON’T KNOW | | 0  1  88 |  | DRINK2_P2 |
| Q1546 | | While you were in a sexual relationship with PARTNER 2, did you have sex with anybody else? | NO  YES | | 0  1 |  | SXCUR_P2 |
| Q1547 | | As far as you know, during the time you were having a sexual relationship with PARTNER 2, do you think PARTNER 2 had sex with other people? | NO  YES | | 0  1 |  | MCP_P2 |
| Q1548 | | How confident are you that you can use a condom with PARTNER 2? | VERY CONFIDENT  SOMEWHAT CONFIDENT  NOT AT ALL CONFIDENT | | 1  2  3 |  | UCND_P2 |
| Q1549 | | How confident are you that you can discuss HIV with PARTNER 2? | VERY CONFIDENT  SOMEWHAT CONFIDENT  NOT AT ALL CONFIDENT | | 1  2  3 |  | TLKHIV_P2 |
| Q1550 | | Have you ever discussed getting an HIV test with PARTNER 2? | NO  YES | | 0  1 |  | TLKTST_P2 |
| Q1551 | | Have you ever gone together with PARTNER 2 for an HIV test? | NO  YES | | 0  1 |  | TOGTST_P2 |
| Q1552 | | Has PARTNER 2 shared the results of their HIV test in the past 12 months? | NO  YES | | 0  1 |  | TSTDISC_P2 |
| Q1553 | | In the past 12 months, has PARTNER 2 ever hit, slapped, kicked, pushed, shoved or otherwise physically hurt you? | NO  YES | | 0  1 |  | VICVIO_P2 |
| Q1554 | | In the past 12 months, have you ever hit, slapped, kicked, pushed, shoved or otherwise physically hurt PARTNER 2? | NO  YES | | 0  1 |  | PERVIO_P2 |
| PARTNER #3 | | | | | | | |
| Q1555 | | Tell me about another person you had sex with most recently before PARTNER 2. What is the nickname or initials I could use to talk about this person? | PARTNER #3 | |  |  | NAME_P3 |

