| Q1556 | | When was the most recent time you had sex with PARTNER 3? | MONTHS __ __  WEEKS __ __  DAYS __ __ | |  |  | RECSEX_P3 |
| Q1557 | | Is PARTNER 3 a man or a woman? | MAN  WOMAN | | 1  2 |  | GEND_P3 |
| Q1558 | | Where did you meet PARTNER 3? | SCHOOL  WORK  MY CAMP  ANOTHER CAMP  MOSQUE/CHURCH  STREET  CLUB/BAR  GUEST HOUSE  BEACH  PARTY  WEDDING/FUNERAL  OTHER___________________ | | 1  2  3  4  5  6  7  8  9  10  11  12 |  | MEET_P3  METP1_S |
| Q1559 | | How long have you been having sex with this partner? | YEARS_________________  MONTHS_______________  WEEKS_________________ | |  |  | SEXDY_P3  SEXDM_P3  SEXDW_P3 |
| Q1560 | | What type of relationship do you have with PARTNER 3? | SPOUSE  POLYGAMOUS SPOUSE  COHABITING PARTNER  GIRLFRIEND/BOYFRIEND  FRIEND  CASUAL ACQUAINTANCE  COMMERCIAL SEX WORKER  ONE TIME PARTNER  OTHER___________________ | | 1  2  3  4  5  6  7  8  9 |  | RELP_P3  RELP_P3_S |
| Q1561 | | (If needed: To the best of your knowledge) How old is _____ PARTNER 3)? | __ __ YEARS | |  |  | AGE_P3 |
| Q1562 | | Is PARTNER 3 a member of this camp? | NO  YES  DON’T KNOW | | 0  1  88 |  | CAMPM_P3 |
| Q1563 | | Are you still having sex with PARTNER 3? | NO  YES | | 0  1 |  | SEXCUR_P3 |
| Q1564 | | How often do/did you have sex with PARTNER 3? | EVERY DAY  A FEW TIMES A WEEK  FEW TIMES A MONTH  ABOUT ONCE A MONTH  ONLY 1-2 TIMES EVER | | 1  2  3  4  5 |  | SEXFRQ_P3 |
| Q1565 | | During the last (most recent) time you had sex with this partner, did you use a condom? | NO  YES  DON’T KNOW | | 0  1  88 |  | CNDUSE_P3 |
| Q1566 | | How many times would you say you had sex with PARTNER 3 during the last one month you had sex with him/her? | _____________ | |  |  | NUMSEX_P3 |
| Q1567 | | Of these (Response from Q1566) times, how many times would you say you used a condom? | _____________ | |  |  | NUMCND_P3 |
| Q1568 | | Did you ever give PARTNER 3 money in exchange for having sex with you? | NO  YES | | 0  1 |  | GIVFSP_P3 |
| Q1569 | | Did PARTNER 3 ever give YOU money in exchange for having sex? | NO  YES | | 0  1 |  | RECFSP_P3 |
| Q1570 | | Did you use a condom the last time money was given or exchanged for sex with PARTNER 3? | NO  YES | | 0  1 | **ASK ONLY IF either Q1570 or Q1571 =1** | CNDM_P3 |
| Q1571 | | The last time you had sex with PARTNER 3, did you drink alcohol before or during sex | NO  YES | | 0  1 |  | DRNK1_P3 |

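### As printed, the Q107 skip in Appendix D sends childless respondents past the asset and camp-role questions, and several later survey filters point to the wrong items.

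*Protocol*

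**What the plan says.** All the items are in the questionnaire at Appendix D. Section 8.2.3 (Behavioral Survey) says this form serves baseline and the 12- and 30-month follow-ups.

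- **Q107** reads "How many children have you had". Its code, skip and variable cells read "0 | Q111 | CHILD_EV": code 0 (NO CHILDREN) goes to Q111.
- **Q108**, next in order, asks how many of the children are alive. **Q109** asks "Do you own any of the following items" and lists ten goods. **Q110** asks "What is your role in this camp". **Q111** turns to other camps visited.
- **Q1407** asks "How many of these partners were women and how many were men" and is conditioned on Q100 = 1.
- **Q1543** asks "Did you use a condom the last time money was given or exchanged for sex with PARTNER 2" and is conditioned on Q1542 or Q1543.
- **Q1570** asks "Did you use a condom the last time money was given or exchanged for sex with PARTNER 3" and is conditioned on Q1570 or Q1571.
- **Q1241**, inside the Friend 2 block, asks "Do you think FRIEND 1 gets hit by her sexual partner".

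**The concern.** A skip should pass over only the questions that its trigger makes meaningless. Having no children makes Q108 meaningless, but says nothing about owning a radio or being camp treasurer. As printed, whether assets and camp role are recorded is decided entirely by fatherhood.

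That kind of gap is hard to repair afterwards. Among childless men no asset or role value is observed at that wave. A complete-case model that included either variable would drop all of them, and an imputation model would have to borrow the relation from men with children. Section 9.1.5 plans for missing data arising from loss to follow-up, not for gaps built into the form. Owned goods are a natural baseline descriptor in a microfinance trial, and camp role in a trial that works through camp leaders.

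The faulty filters in Sections 14 and 15 of the form are a smaller, separate matter: they select the wrong respondents for particular items.

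**Working it through.** The protocol gives no figure to reproduce here. The check is a trace of the printed routes, followed by one illustrative count.

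**1. Route at Q107.**
- One or more children: Q107 → Q108 → Q109 → Q110 → Q111.
- No children: Q107 → Q111. Not asked: Q108, Q109, Q110.

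The skip must belong to the childless. 0 is the only code in the row, and sending fathers to Q111 would leave Q108 unasked of the only people it concerns. A table cell displaced in extraction is unlikely, because Q108 carries its own note in the same column.

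**2. What is lost.** Q109 holds ten variables (ASSET_FM to ASSET_CR) and Q110 one coded role (CAMPROLE): 10 + 1 = 11 variables, missing for 100% of childless respondents. No later item repeats them, and the camp roster described in Section 4.3 does not record role. With the skip pointed at Q109, this loss falls to 0% and only Q108 is passed over.

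**3. How many men.** The documents do not give the childless share, so this is an assumption. With the study size of 1249 from the Protocol Summary, affected men = share × 1249:
- 30%: 0.30 × 1249 ≈ 375
- 50%: 0.50 × 1249 ≈ 625
- 70%: 0.70 × 1249 ≈ 874

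Section 3.2.3 gives 1252 instead, which moves these counts by at most about 2 (0.70 × 3 = 2.1).

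**4. Paid-sex condom filters.** The partner 1 block shows the intended pattern: Q1516 is asked if either money item, Q1514 or Q1515, is yes. The partner blocks start at Q1501, Q1528 and Q1555, so each is 27 numbers after the last.

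| Block | Money items | Condom item | Printed filter |
| --- | --- | --- | --- |
| Partner 1 | Q1514, Q1515 | Q1516 | Q1514 or Q1515 |
| Partner 2 | Q1541, Q1542 | Q1543 | Q1542 or Q1543 |
| Partner 3 | Q1568, Q1569 | Q1570 | Q1570 or Q1571 |

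The partner 2 filter is one number too high and the partner 3 filter two too high, which would fit uncorrected renumbering. At Q1543 the self-reference cannot be true before the item is asked, so the filter reduces to Q1542 = 1: a man who paid partner 2 but was not paid by that partner is not asked. At Q1570 the filter cites the item itself and the alcohol question that follows it. Neither money item is tested.

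**5. Remaining slips.** There is no Q100; sex is recorded at Q101. Q1241 names the first friend, although its gate (Q1227) and variable (VVF2) belong to the second.

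**The case against.** The strongest reply is that little of consequence rests on these items, and much of that stands.

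- A reader might infer that assets are the only baseline wealth measure. The form does not support this. Section 16 asks total savings (Q1632) and money owed to the respondent (Q1633), both reached by every printed route. Where applicable it also asks wages (Q1607), business stock (Q1616), profit (Q1617) and debt (Q1630). None of these passes through Q107. They could also inform imputation of assets, although the relation would still be learned from fathers only.
- No named endpoint, mediator or covariate uses Q109 or Q110. Section 9.1.3 allows covariate control where necessary and lists none, so a model that drops every childless man is possible but not planned. The skip is the same in both arms.
- Paid-sex condom use is not a listed outcome. Consistent condom use (Section 7.4.1) rests on counts at Q1512–Q1513, Q1539–Q1540 and Q1566–Q1567, which carry no faulty filter. Partner sex is also asked at Q1503, Q1530 and Q1557, so Q1407 is partly redundant.
- The appendix is a printed form, and the survey runs on tablets. A filter on an absent or self-referring item could hardly be programmed literally. Section 6.2 pre-tests the items and tablet procedures on fifty camp members. Appendix D also lacks sections for some measures in the protocol body, such as gender role conflict and household hunger, so it may not be the final instrument.

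These points limit the importance of the errors; they do not remove them. Section 6.2 names no check of skip logic, and the form attached to the protocol still carries the wrong routes.

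**Conclusion.** The point holds for the form as printed. Every respondent who answers NO CHILDREN at Q107 lacks ten asset variables and camp role at each wave using the form. Q109 is the only measure of owned goods, but not the only economic measure. Both primary endpoints are untouched; what suffers is baseline description and any adjustment or subgroup analysis that uses assets or role. The number of men is unknown, and 375 to 874 illustrates an assumed childless share of 30% to 70%. The filter errors at Q1543 and Q1570 mean that paid-sex condom use for partners 2 and 3 is asked of the wrong men. Q1407 and Q1241 are smaller slips.

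Two stronger readings are not supported. One is that these data were in fact lost: the documents do not show how the tablet version was programmed. The other is that asking again at 12 months would make good the baseline gap: those answers come after randomisation, and the loans may themselves have changed what men own.

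**What to change.** 1. Change the Q107 NO CHILDREN skip from Q111 to Q109.
2. Gate Q1543 on Q1541 or Q1542, Q1570 on Q1568 or Q1569, and Q1407 on Q101.
3. Correct Q1241 to FRIEND 2.
4. Check that the tablet program follows the corrected routes, and record which version ran at each wave.
5. If baseline has already run with the error, report the gap openly. Asset and role questions can still be asked of everyone at later waves as follow-up data, but those answers should not be used as baseline covariates.

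The cost is one skip target, three filters and one label in the form and program, plus about a minute of interview time for each childless respondent. Done before baseline, this avoids the loss; done later, it cannot restore the baseline values.

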***Interviewer:***

→ Now I’d like to ask you a few questions about how you and your fellow camp members get along in this camp. For each statement, please tell me whether you strongly agree, agree, strongly disagree, or disagree with the statement. When answering these questions, keep in mind that I’m asking you to say whether you agree with the statement based on what is true for **you**, not what other people think is true or what your camp thinks is true.

| **No.** | **Questions and Filters** | **Coding Categories** | **Codes** | **Skip to:** | **VARIABLE** |
| --- | --- | --- | --- | --- | --- |
| Q401 | People in my camp are willing to help each other. | STRONGLY AGREE  AGREE  DISAGREE  STRONGLY DISAGREE | 1  2  3  4 |  | SOCOH1 |
| Q402 | We are very close to each other in this camp. | STRONGLY AGREE  AGREE  DISAGREE  STRONGLY DISAGREE | 1  2  3  4 |  | SOCOH2 |
| Q403 | I can trust my fellow camp members. | STRONGLY AGREE  AGREE  DISAGREE  STRONGLY DISAGREE | 1  2  3  4 |  | SOCOH3 |
| Q404 | The members of my camp get along with each other. | STRONGLY AGREE  AGREE  DISAGREE  STRONGLY DISAGREE | 1  2  3  4 |  | SOCOH4 |
| Q405 | The members of my camp share the same values. | STRONGLY AGREE  AGREE  DISAGREE  STRONGLY DISAGREE | 1  2  3  4 |  | SOCOH5 |

Section 5: Collective Efficacy

